# Design of the STEPS trial: a phase II randomized controlled trial evaluating eHealth-supported motor-cognitive home training for Parkinson’s disease

**DOI:** 10.1186/s12883-023-03389-y

**Published:** 2023-10-04

**Keywords:** Parkinson’s disease, eHealth, Home exercise, Physical activity, Motor-cognitive exercise

## Abstract

**Background:**

Electronic health (eHealth) technology offers the potential to support and motivate physical activity for symptom management in Parkinson’s disease (PD). It is also recommended that motor exercise in PD be complemented with cognitive training aimed at attentional or executive functions. This paper describes the protocol for a double-blind randomized controlled trial to evaluate the effects of motor-cognitive training in the home environment, supported by eHealth.

**Methods/design:**

The Support for home Training using Ehealth in Parkinsons diseaSe (STEPS) is a double-blind single center randomized controlled trial. Two parallel groups will include in total 120 participants with mild to moderate PD who will receive either (i) the intervention (a progressive 10-week individualized motor-cognitive eHealth training with cognitive behavioral elements to increase physical activity levels) or (ii) an active control group (an individualized 10-week paper-based home exercise program). The active control group will not receive motor-cognitive exercises or cognitive behavioral approaches to increase physical activity level. The primary outcome is walking capacity assessed by the six-minute walk test (6MWT). Secondary outcomes will include gait performance during single and dual task conditions, gait speed, functional mobility and lower limb strength, balance, physical activity behavior and a range of patient reported outcome measures relevant in PD.

**Discussion:**

The STEPS trial will answer the question whether 10 weeks of eHealth supported motor-cognitive exercise in the home environment can improve walking capacity in PD when compared to a standard paper exercise program. Findings from this study will also strengthen the evidence concerning the efficacy of PD-specific eHealth interventions with a view meeting future health care demands by addressing issues of inaccessibility to specialized neurological rehabilitation in PD.

**Trial registration:**

ClinicalTrials.gov August 2022, NCT 05510739.

**Supplementary Information:**

The online version contains supplementary material available at 10.1186/s12883-023-03389-y.

## Background

 People living with Parkinson’s disease (PD) are typically less physically active than their healthy counterparts. Deteriorations in walking ability occur in line with disease progression, and reductions in gait speed and behavior are strong indicators of advancing disability [1, 2]. The merits of exercise for the treatment of gait and balance impairments in PD have been established [3–5]. Although questions remain concerning optimal exercise type, intensity and duration, high dose exercise appears to have greater effects on motor symptoms [6–8]. It is also recommended that motor training in PD be complemented with cognitive training aimed at attentional or executive functions [9]. Systematically collated evidence suggests that motor-cognitive, or dual task exercise paradigms, provide positive effects on motor features [10, 11], as well as improve dual-task performance [12]. The simultaneous combination of physical and cognitive exercise is assumed to exert synergistic responses in a process where the physical challenge ‘facilitates’ neurological responses and the cognitive challenge serve to ‘guide’ these neuroplastic processes [13, 14].

People can live with PD for several decades - a vast majority of whom live in their own home [15], and require therefore continual access to specialised neurological treatment and rehabilitation, throughout all disease stages. An added challenge for people with PD, is that sustaining exercise levels is often hindered by dopamine deficiency and evolving neuropsychiatric symptoms which in turn reduce initiative-taking [16]. Notably, despite a range of disease-related motor impairments, people with PD commonly report psychological symptoms such as anxiety, depression and low self-efficacy as major barriers to adherence to home exercise [17, 18]. It is therefore advocated that cognitive-behavioural elements be incorporated when aiming to change a person’s physical activity behaviour in the long term [19]. Such support has been successfully delivered using motivational apps in PD populations which have aimed to increase physical activity participation in daily life [20, 21].

Electronic health (eHealth) technology offers the potential to support and motivate motor-cognitive exercise as a part of everyday life with PD [22, 23]. There is also strong evidence for the efficacy of telehealth and exergame-based interventions to improve motor symptoms [24, 25]. Tablet and smartphone-based software applications have become popular means of supporting exercise among older adults and in PD [26, 27], a process further accelerated during the Covid-19 pandemic [28]. However, due to the complex nature of PD symptoms, this group requires disease-specific, as opposed to generic training applications [29]. Additionally, the core components and dose of motor-cognitive and exergame-based interventions are generally vaguely described in the literature, which inhibits interpretation and replication of findings [29]. Taking these factors into consideration, we designed a disease-specific motor-cognitive home-based intervention for PD which we subsequently tested in a feasibility study. In short, results showed the intervention to be safe and feasible in terms of recruitment capability, acceptability, and demand. Results also showed that the intensity of the level of motor challenge needed to be increased prior to efficacy testing (manuscript under review).

Here we describe the study protocol of the Support for home Training using eHealth for Parkinson’s diseaSe (STEPS) trial. STEPS is designed as a digitally supported non-supervised home-based exercise intervention. A unique element of this intervention involves the use of eHealth technology to integrate motor-cognitive exercises, which alongside cognitive behavioral techniques aims to increase physical activity behavior.

### Objectives

The primary objective of the STEPS study is to evaluate whether a motor-cognitive home exercise program, targeting functional strength and exercise capacity, can improve walking capacity in PD. Secondary objectives will be to investigate whether the intervention will result in improvements in other clinically relevant outcomes such as, physical activity participation, dual-task capacity during walking, health-related quality of life, and exercise self-efficacy. In conjunction with assessment procedures, we will also explore the added benefit of the use of inertial sensors during standard tests of gait capacity in a primary care setting.

Our underlying hypothesis is that the motor-cognitive eHealth supported home training program will be more effective than the active control condition in improving walking capacity over a 10-week period. Additionally, we hypothesize that motor-cognitive intervention will lead to improvement in dual task performance.

## Methods

### Ethical approval and trial registration

This study has been approved by the Swedish Ethical Review Authority (Dnr: 2022-02979-01 and 2023-00717-02). The STEPS trial was registered on Clinicaltrials.gov in August 2022 (NCT 05510739). All participants will receive written and verbal information regarding study details, prior to giving their written consent for participation in the study.

### Study design and setting

The STEPS trial is a randomized controlled, double blind intervention study which will occur at one clinical site. All participant assessments will occur in a primary care rehabilitation setting in Stockholm, Sweden. In Sweden, patients can receive out-patient physiotherapy treatment without doctor/specialist referral. Following assessment, participants will be randomized to either (i) the intervention (motor-cognitive eHealth training) or to (ii) an active control group (individualized home exercise program). Participants will be blinded, i.e., not made aware, of the hypothesized relative merits of the different group conditions. Training will occur in the home environment for a 10-week period. Planning and development of the STEPS study was informed by the existing literature pertaining to designing and evaluating successful mobile technologies for the management of chronic conditions among community-dwelling older adults [30]. Two specific best-practice approaches which we implemented involved application of a user-centered design, as well as use of an interdisciplinary approach. More specifically, at project onset, we recruited a group of end-users − people with PD, both men and women at varied ages and stages of the disease – who informed and gave feedback to the research group throughout the design and feasibility stages of the eHealth intervention. This iterative process informed specific decisions regarding intervention content as well as hardware and software features. Additionally, several members of the research group are physiotherapist researchers with experience of designing PD exercise interventions. We also used an interdisciplinary approach involving collaboration with Occupational therapists in a preparatory investigation of technology use among people with PD [31] and a Neuropsychologist regarding the design of PD-specific cognitive components of the motor-cognitive exercises, as well as technical experts regarding software interface aspects. The SPIRIT guidelines (2013) have guided the formation of this protocol manuscript.

### Study population

This intervention will target community-dwelling people with mild to moderate idiopathic PD, who are in need of support to increase their levels of physical activity in everyday life. This home exercise intervention is hypothesized to incur greater beneficial effects for sedentary individuals or those engaging in lower levels of physical activity [32], than that which is recommended for the maintenance of health. For this reason, recruitment advertisement materials will especially target those who are less physically active and require support to increase their physical activity levels. Inclusion and exclusion criteria (outlined in Table 1) are aimed to incorporate typical patients across a spectrum of functional capacity at mild to moderate PD stages. To ensure cognitive status enabling adherence to the study protocol, participants with severe cognitive impairment, operationalized with the MoCA, will be excluded [33]. Exclusion criteria are motivated primarily as safety measures to offset possible adverse events which can occur during unsupervised motor-cognitive training in the home-environment.

### Screening and recruitment

Participants will be recruited using a varied approach through advertisement in patient organization publications, by distributing ethically approved study flyers to neurologists/ rehabilitation practitioners and by advertisement on social media platforms managed by the responsible academic (Karolinska Institutet) and clinical sites (Primary Care Rehabilitation at Stockholm Sjukhem, Sweden). The recruitment process will occur systematically in the following sequence: Potential participants who have registered interest in the study will be contacted by study coordinators for an initial telephone interview. After the telephone screening, eligibility of potential participants will be established at an in-person clinical assessment. Prior to the assessment, potential participants will receive verbal and written information of study procedures and be given the chance to pose questions. Recruitment will occur in three to four successive waves, consisting of 30–40 participants per wave. Participants will be randomly assigned in a 1:1 ratio to the intervention or control groups. Participants in both groups will be encouraged to continue their usual daily activities during the 10-week period between measurements. They will however be advised against participating in parallel research studies aiming to affect health or adjusting their PD medication during the 10-week period.

**Table 1 Tab1:** Inclusion and exclusion criteria

Inclusion criteria	Exclusion criteria
Idiopathic Parkinson’s disease	No internet connection in the home
Hoehn & Yahr stage 1 - 3	Pre-existing orthopedic or neurological diseases affecting gait
Montreal Cognitive Assessment score ≥ 21 points	Visual or hearing impairments impeding intervention delivery
Age ≥ 50 years	≥ 2 falls one month prior to inclusion
Able to walk independently indoors for six minutes without a walking aid.	

### Randomization and blinding

Randomization to the respective groups will be performed by a person in the research team who is not involved in assessment or training procedures. Allocation to the two groups will be performed in a 1:1 ratio, using web-based randomization software (randomization.com). Participants, assessors, and those performing data analysis will be blinded for group allocation. The rigor of the blinding procedure will be evaluated following post-assessment, by asking assessors to fill in a questionnaire where they report their blinding beliefs [34].

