### Primary outcome measure

The six-minute walk test (6MWT) is the primary outcome measure to assess efficacy of the intervention to improve walking capacity in PD. This test of walking capacity is reliable and valid for use in older adults and in PD [35, 36]. Participants are instructed to cover as much distance as possible, by walking back and forth between two cones placed 30 m apart, during a 6 minute interval. Participants will rate their perceived exertion and level of breathlessness using the Borg RPE and Borg CR-10 scales respectively, before and after the test [37]. When compared to healthy controls of similar age, people with PD walk at lower gait speed and with shorter stride lengths during the six-minute walk [38]. The distance covered during this test is also related to PD motor features such as bradykinesia and impaired balance [39].

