### Intervention group condition

Participants in the intervention group will perform exercise guided by videos in a mobile application, viewed on a digital tablet three times per week. Baseline assessment will determine the level of motor difficulty (three levels) and cognitive dual task difficulty (two levels) that each participant will be assigned to. Assignment to level of motor difficulty will be decided on a case-to-case basis by the research team and be guided by participants baseline performance and (1) self-reported ability to transfer from floor to chair, (2) balance performance using the Mini-BESTest, and (3) usual gait speed measured during the 6MWT. Assignment to the level of difficulty of the cognitive dual tasks will be guided by (1) global cognition using the MoCA, and (2) performance (completion time, safety during transfers and turning, and performance on the serial subtraction task) during the TUG cog. The initially assigned levels of motor/ cognitive challenge can be altered during the training period if deemed appropriate.

Following randomization, a researcher not involved in assessments will perform a home visit or digital visit among participants to establish the safety of the home exercise environment. Short- and long-term goals regarding increasing physical activity behavior will be discussed, decided and documented during the home/digital visit. Progress towards attainment of the short-term goals will be followed up mid-intervention (5 weeks) and post-intervention (11 weeks). Commercial waist-worn pedometers (Rubicson) will be distributed for participants to track physical activity behavior (steps per day) during the intervention period. Long term physical activity goals and objective physical activity behavior will be assessed one year post intervention. The process of designing behavioral change components of the intervention was guided by an evidence-based behavioral change framework characterizing essential components of behavioral change [55] and involved elements such as, education, goal setting, goal reflection, self-monitoring and reflection, as well as digital support.

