### Control group condition

Participants in the control group will receive a paper printout with home exercises to be performed three times per week. The home exercise program will be instructed by a physiotherapist at an in-person visit scheduled after baseline assessments. Level of motor difficulty (three levels) will be decided by the same criteria as in the intervention group. The exercises will focus on functional strength, flexibility, and balance. Written information on how exercises can be progressed will be included, but no support for progression will be given during the training period. Should participants in the active control group have further questions or concerns regarding their exercise program, they will be able to contact their physical therapist by telephone.

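### Participants are described as blinded to allocation, but they are blinded only to the study hypothesis; the allocation statement and the double-blind label need correcting

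*Protocol article*

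**What the plan says.** The protocol article describes blinding in four places.

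- Randomization and blinding makes the strongest statement: "Participants, assessors, and those performing data analysis will be blinded for group allocation". The check of blinding is made after post-assessment "by asking assessors to fill in a questionnaire where they report their blinding beliefs".
- Study design and setting labels the trial: "The STEPS trial is a randomized controlled, double blind intervention study which will occur at one clinical site". It then says what this means for participants: "Participants will be blinded, i.e., not made aware, of the hypothesized relative merits of the different group conditions".
- The Abstract, under Methods/design, says that STEPS "is a double-blind single center randomized controlled trial".
- The Abstract, under Background, also uses the double-blind label.

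On the programmes themselves, Intervention group condition says "Participants in the intervention group will perform exercise guided by videos in a mobile application, viewed on a digital tablet three times per week", and Control group condition says "Participants in the control group will receive a paper printout with home exercises to be performed three times per week". For the primary outcome, the six-minute walk test (6MWT), Primary outcome measure says "Participants are instructed to cover as much distance as possible". According to Secondary outcome measures, participants complete all questionnaires at home.

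**The concern.** Blinding to allocation and blinding to the hypothesis protect against different things. A participant blinded to allocation does not know which treatment they have. A participant blinded to the hypothesis knows what they have but has not been told which option is expected to win. The second is weaker: it may reduce expectation effects, but it leaves participants free to form their own view of the programme they were given.

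This matters because participants' own effort and judgement enter the outcomes. 6MWT distance depends on how hard the participant tries, which a blinded assessor cannot control. For the self-rated instruments (EQ-5D, PDQ-39, Walk-12G, ABC, S-ESS, HADS) the participant is the one who assesses. A reader who relies on the double-blind label or on the allocation sentence would give these results more credit for protection against expectation than the design earns.

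**Working it through.** The point turns on comparing statements, so no calculation decides it.

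1. **What is claimed.** Randomization and blinding names three parties (participants, assessors, analysts) and one object, group allocation. Because participants are named, the sentence cannot be read as meaning assessors and analysts alone.

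2. **What is done.** Study design and setting gives the only description of how participants are blinded: they are not told which condition is thought better. That is a different object from allocation, so the two sections disagree.

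3. **Whether the claim could be true.** The arms can be compared from Intervention group condition, Control group condition and Table 2.
   - Intervention: video-guided application on a tablet, pedometer, short- and long-term activity goals, cognitive dual tasks, at least 60 minutes of walking a week, and remote support (weekly for the first five weeks, by chat or telephone, and more when needed).
   - Control: a paper printout taught in person by a physiotherapist, with none of the components just listed; participants can telephone their physiotherapist with questions.

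   No participant could be unaware of which of these they are following. The allocation statement is therefore wrong for participants, and the hypothesis-only description is the one that fits the design.

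4. **Which outcomes are touched, and how.**
   - Self-rated, completed at home: EQ-5D, PDQ-39, Walk-12G, ABC, S-ESS and HADS, six instruments. The rater knows the programme, so these are not blinded.
   - Performance tests, including the primary 6MWT: conducted by physical therapists (Data collection) who are stated to be blinded, on participants who know their programme. These are assessor-blinded.

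5. **What is checked.** Only the assessors' blinding beliefs are described as being collected. No participant check of hypothesis blinding is described.

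6. **Effect on the plan's figures.** None. The stated 58 per group uses a 50 m difference, SD 107.09 m, one-sided 5% and 80% power. The normal approximation gives 2 × (1.645 + 0.842)² × (107.09/50)² = 56.7, so 57, and the t-test calculation gives 58 as stated. Blinding is not an input to any of these.

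**The case against.** The best defence is that the article is open about what it means. Study design and setting uses the double-blind label and defines participant blinding in the same section, and Table 2 lists every visible difference between the arms. Participants cannot be masked to an exercise programme, and the trial does what it reasonably can. The control is active and individualised, with three sessions a week, three motor levels and in-person instruction. The hypothesis is withheld, assessors and analysts are blinded, and physical activity is recorded by accelerometer. All of this stands, and it makes the fault one of description, not concealment. It does not rescue the allocation sentence, which says something different and untrue. Nor does condensation into an article explain it, since this is a wrong statement and not an omission.

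A reader might infer several stronger points that the document does not support:

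- *The whole trial is open-label.* Not for the 6MWT and other performance tests, whose assessors are stated to be blinded.
- *The Abstract claims blinding to allocation.* It says only that the trial is double-blind; the allocation claim stands in one sentence of Randomization and blinding.
- *Participant expectation is never measured.* Both groups receive a questionnaire on their perceptions of the programmes after the 10 weeks (Secondary outcome measures). Its items are not shown, so this cannot be established.
- *The extra attention in the intervention arm is a blinding failure.* Goal setting, self-monitoring and support are declared parts of the intervention, and masking would not remove them.
- *The false-positive rate is inflated by a known amount.* The document gives no size for expectation bias, so any such figure would only reflect the bias assumed.
- *The registration is wrong.* The registry entry is not shown.

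**Conclusion.** The concern holds as a correction to how the design is described. One sentence asserts participant blinding to allocation, another section shows that participants are blinded only to the hypothesis, and the arms cannot be masked from those in them. The double-blind label in three places (Abstract Background, Abstract Methods/design, Study design and setting) shares the problem.

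The reach is the interpretation of the primary outcome and six self-rated instruments. The size of any resulting bias is unknown and may be small, given the active control and the withheld hypothesis. The design and analysis stand, and no sample size, alpha or power figure moves. The conclusion assumes only that participants can tell a tablet-based programme from a paper one, and that assessor and analyst blinding operates as stated.

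**What to change.** **Wording.** In Abstract Background, Abstract Methods/design, Study design and setting, and Randomization and blinding, describe the trial as assessor- and analyst-blinded, with participants unaware of the study hypothesis only. Remove participants from the sentence on allocation.

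**Reporting.** Present EQ-5D, PDQ-39, Walk-12G, ABC, S-ESS and HADS as not blinded. Present the 6MWT and the other performance tests as assessor-blinded with participants aware of their programme. State possible expectation effects as a limitation.

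**Registration.** Check that its masking entry agrees with the corrected description.

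**Optional.** If the post-programme perceptions questionnaire has no such item, one could be added asking which programme the participant believed was expected to work better, and reported by arm.

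**Cost.** The required changes are to wording and reporting, and the design label becomes less favourable. The optional item has two drawbacks: asked after training, it mixes expectation with perceived benefit, and it may prompt participants to guess the hypothesis before the one-year physical activity assessment. If assessments are already complete, the wording and reporting changes still apply.
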